## Abstract

**Background:**

The World Health Organization targeted trachoma for global elimination as a public health problem by 2030. Reaching elimination thresholds by the year 2030 in the Republic of South Sudan will be a considerable challenge, as the country currently has many counties considered hyper-endemic (> 30% trachomatous inflammation-follicular [TF]) that have yet to receive interventions. Evidence from randomized trials, modeling, and population-based surveys suggests that enhancements may be needed to the standard-of-care annual mass drug administration (MDA) to reach elimination thresholds in a timely manner within highly endemic areas. We describe a protocol for a study to determine the cost and community acceptability of enhanced antibiotic strategies for trachoma in South Sudan.

**Methods:**

The Enhancing the A in SAFE (ETAS) study is a community randomized intervention costing and community acceptability study. Following a population-based trachoma prevalence survey in 1 county, 30 communities will be randomized 1:1 to receive 1 of 2 enhanced MDA interventions, with the remaining communities receiving standard-of-care annual MDA. The first intervention strategy will consist of a community-wide MDA followed by 2 rounds of targeted treatment to children ages 6 months to 9 years, 2 weeks and 4 weeks after the community MDA. The second strategy will consist of a community-wide biannual MDA approximately 6 to 8 months apart. The costing analysis will use a payer perspective and identify the total cost of the enhanced interventions and annual MDA. Community acceptability will be assessed through MDA coverage monitoring and mixed-methods research involving community stakeholders. A second trachoma-specific survey will be conducted 12 months following the original survey.

**Discussion:**

ETAS has received ethical clearance and is expected to be conducted between 2022 and 2023. Results will be shared through subsequent manuscripts. The study’s results will provide information to trachoma programs on whether enhanced interventions are affordable and acceptable to communities. These results will further help in the design of future trachoma-specific antibiotic efficacy trials. Enhanced MDA approaches could help countries recover from delays caused by conflict or humanitarian emergencies and could also assist countries such as South Sudan in reaching trachoma elimination as a public health problem by 2030.

**Trial registration:**

This trial was registered on December 1^st^, 2022 (clinicaltrails.org: NCT05634759).

**Supplementary Information:**

The online version contains supplementary material available at 10.1186/s12886-023-02783-x.

## Background

The World Health Organization (WHO) has targeted trachoma for global elimination as a public health problem by 2030 (trachomatous inflammation-follicular [TF] < 5% among children ages 1 to 9 years; and trachomatous trichiasis [TT] < 0.2% in those 15 years and older) [1]. Although progress has been made in reducing the burden of trachoma in many endemic countries, some countries are experiencing persistently endemic trachoma after many years of interventions, and countries affected by conflict and humanitarian emergencies could take decades to reach trachoma elimination targets [2, 3]. The “A” component of the WHO-endorsed SAFE (surgery, antibiotics, facial cleanliness, and environmental improvement) strategy focuses on mass drug administration (MDA), particularly with azithromycin, targeting all members of an endemic district where the prevalence of active trachoma is ≥ 5% among children ages 1 to 9 years.

Evidence for the importance of enhanced MDA strategies is growing, particularly with the help of modeling studies [4, 5]. Recent work by the Neglected Tropical Disease (NTD) Modelling Consortium has demonstrated that in some hyperendemic districts and countries, standard-of-care annual community-wide MDA will not result in a district reaching the elimination of trachoma as a public health problem threshold within 10 years [5]. Fortunately, models have projected that alternative enhanced MDA strategies can change the annual trajectory of trachoma prevalence [5]. They have suggested that 1 alternative strategy, characterized by a community-wide MDA followed by 2 extra rounds of treatment to children ages ≤ 9 years, could lead to elimination faster compared to standard-of-care annual MDA. Empirical data from endemic communities under different alternative MDA strategies are needed to verify these modeling results.

The Republic of South Sudan has historically had one of the highest burdens of trachoma in the world [6, 7]. While the South Sudan Ministry of Health (MOH) has been implementing the SAFE strategy in various counties (the equivalent of districts) throughout the country for over 10 years, there remain many counties considered to be hyper-endemic (> 30% TF). Furthermore, a considerable proportion of the country has not yet been assessed for trachoma prevalence, and thus interventions have not yet started. Eliminating trachoma as a public health problem by the year 2030 in South Sudan will be a considerable challenge [7].

This proposed study will estimate the cost and community acceptability of enhanced MDA strategies in South Sudan, which along with the trachoma survey data from this study will be important for the future planning and design of comparative efficacy trials. If efficacious and cost-effective, enhanced MDA approaches could help countries recover from delays in programming caused by conflict, humanitarian emergencies, or COVID-19; and could also assist countries, including South Sudan, in reaching trachoma elimination as a public health problem within years instead of decades [5]. This has the potential to not only reduce disease burden precipitously but also could result in significant cost savings over the long term to countries and donors.

## Methods

### Study design overview

The Enhancing the A in SAFE (ETAS) study is a community randomized study to evaluate cost and community acceptability of enhanced antibiotic trachoma interventions within an endemic county in South Sudan. A population-based prevalence survey will be conducted whereby 30 communities are selected for trachoma assessment. Following the survey, communities will be randomized 1:1 to receive 1 of 2 enhanced antibiotic interventions (Fig. 1). The remaining communities in the county will receive standard-of-care annual MDA. The primary outcomes of the study are the cost of enhanced MDA compared to standard-of-care annual MDA and the community acceptability of enhanced MDA within study communities. A trachoma impact survey will be conducted approximately 12 months following the original trachoma prevalence survey. The total study duration will be approximately 13 months from the start of the community-level census to the time of the 12 month follow up impact survey. This protocol adheres to the Standard Protocol Items: Recommendations for Interventional Trials (SPIRIT) guidelines and refers to version 1.2 of the study protocol as revised 5 May 2021.

**Fig. 1 Fig1:**
[figure not shown]
ETAS study design summary for communities included in the primary outcome analysis. HH = Household; MDA = Mass Drug Administration

### Setting, eligibility, and participants

The study will be conducted within a trachoma endemic county in Eastern Equatoria state, South Sudan (Fig. 2). This area was chosen based on previous survey data demonstrating a high burden of TF among children ages 1 to 9 years ranging from 30 to 48% [7]. The baseline for this study will be timed to coincide with the scheduled programmatic trachoma impact surveys in Eastern Equatoria state. For purposes of this manuscript, the initial survey connected to this study will be referred to as a baseline survey and the survey conducted at completion of the study will be referred to as an impact survey (survey methods described below). As part of the baseline survey to determine TF prevalence in the study county, 30 communities will be randomly selected from a geographically ordered list provided by the South Sudan MOH Trachoma Control Program [8]. All 30 communities will be enrolled in this randomized community study. Communities are eligible to participate if they are in the study county regardless of the individual-community level TF prevalence. There are no exclusion criteria for community-level participation. Within study communities, all households and individuals will be eligible for participation. Children ages 6 months to 1 year will be eligible for azithromycin interventions in this study as they are normally targeted with this medication as part of programmatic interventions and in previous randomized trials, they could potentially serve as an infection reservoir if not treated and are an age group which may benefit from the ancillary effects of azithromycin on mortality [9–13]. Because of the observed mortality benefit to these young children, ongoing studies are now randomizing children in this age group to multiple doses of azithromycin per year at national levels [14].

**Fig. 2 Fig2:**
[figure not shown]
ETAS study area in Eastern Equatoria state, South Sudan with 2015 TF prevalence estimates shown

For the 30 communities enrolled in the randomized community study, we expect an average population per community (based on programmatic data) of 649 individuals. This would lead to MDA treatment data on approximately 19,470 individuals of all ages. Since children ages 6 months to 9 years account for approximately 40% of the population, we expect to have MDA treatment data on 260 children per cluster or 7,788 total children in this age range.

### Interventions

Antibiotic interventions will take place at the community level. The first intervention strategy will consist of an enhanced antibiotic regimen comprised of a community-wide MDA, followed by 2 additional rounds of targeted treatment to children ages 6 months to 9 years. The targeted treatments will be distributed 2 weeks and 4 weeks after the community-wide treatment, resulting in 3 doses to children 6 months to 9 years. The second strategy will consist of a community-wide biannual MDA approximately 6 to 8 months apart, resulting in 2 doses for the targeted community. Timing of the second dose will be based on access to communities and at least 6 months after the first dose.

Azithromycin, also known in the global trachoma program by the brand name Zithromax®, is a macrolide antibiotic and is used in the treatment of active trachoma. Zithromax® is donated to the South Sudan MOH for MDA by Pfizer Inc., through the International Trachoma Initiative (ITI). The recommended dosage for the treatment of trachoma is a single dose of 20 mg/kg of body weight and is implemented using an “age-height” based dosing strategy for the trachoma MDA campaigns. Azithromycin can be administrated in either tablet form or powder for oral suspension (POS). Dosing and administration for this study will be conducted following procedures outlined in the Zithromax® Management Guide [15]. To reduce the risk of choking, all children participating in the study intervention ages 6 months to 9 years will receive azithromycin by POS only. Populations ineligible for azithromycin based on national guidelines, including infants under 6 months of age, pregnant women in their first trimester, individuals with a previous history of severe adverse events (SAEs), and individuals with severe illness at the time of MDA, will be offered treatment with 1% tetracycline eye ointment (TEO), to be applied twice daily to both eyes for a 6-week period [15]. Trained drug distributors will facilitate drug administration for the appropriate treatment dose by assessing everyone that presents. Those receiving antibiotic will be directly observed by the distribution team.

Throughout this study, existing S, F, and E interventions will continue through standard programming. This includes offering surgery to individuals identified as needing TT surgery, and advocacy work with water, sanitation, and hygiene (WASH) focused non-governmental organizations operating in the country.

### Adverse events

Azithromycin is generally well tolerated and adverse events are rare [16–18]. The most commonly reported side effects of azithromycin are gastrointestinal effects which include diarrhea, nausea, abdominal pain, and vomiting. As part of MDA training, all drug distributors, community chiefs, and government supervisors are trained on side effects and how to respond to SAEs. All study participants will be informed of potential side effects of azithromycin and screened for any history of SAEs from azithromycin. All drug recipients will be informed to immediately report to the drug distributors or community chief if they experience signs and symptoms of any SAE. All suspected SAEs will be recorded, immediately managed via the nearest health facility, investigated, and reported according to South Sudan MOH guidelines and will be recorded using an SAE reporting form. SAEs will be reported to The Carter Center, Pfizer Inc., and the Institutional Review Boards (IRB) within 24 h. An SAE officer will be stationed within the study area for the duration of the project to monitor reports and assist key government staff in investigating and facilitating rapid responses to suspected SAEs during the intervention period. While this study will include increased intensity of antibiotic pressure, Chlamydia-specific antimicrobial resistance to azithromycin has yet to be demonstrated as part of trachoma MDAs, including those with multiple rounds per year [19].

### Treatment masking

Because of the community nature of the MDA treatments, masking will not be possible in this study. However, MDA treatment teams will be different from teams collecting trachoma indicator data. Laboratory and photographic grading team members will be masked to the treatment arm of the study.

### Intervention costing

The costing analysis will determine the relative costs of the enhanced MDA strategies, including the triple dose and biannual MDA, which will be compared to each other, and compared to the standard-of-care annual MDA. This study will utilize the Global Health Cost Consortium Reference Case for Estimating the Costs of Global Health Services and Interventions and the Global Health Cost Consortium Principles and Methods Reporting Checklist to ensure the quality and comparability of results [20, 21]. The costing analysis will provide the evidence base to inform resource allocation decisions by the South Sudan MOH and partners within the country.

The study will take a payer perspective and encompass the costs incurred by The Carter Center as the technical and financial supporting implementing partner. This will be used to identify the cost per person treated and total costs associated with each arm of the study and annual MDA. To reduce the potential for bias, cost data will be collected using the same methods from 15 randomly selected communities in the study county receiving the standard-of-care annual MDA. Taking an ingredients-based approach, the study will include a detailed micro-costing database that captures all financial and economic costs incurred. The study will use the community level as the unit of analysis for total costs and calculate the unit cost per person treated using a top-down approach, dividing the total cost by the number of people treated.

The quantity and price of all required resources will be identified to evaluate total intervention costs for each arm of the study as well as the standard-of-care annual MDA (Table 1). To ensure costs such as salaried labor are not double counted, some activities that include staff time, including social mobilization and training, will not be broken down into all specific components. Salaried costs, for example, will be included under central administration and not included in each cost category. Where possible, data will be extracted from The Carter Center and South Sudan MOH databases.

**Table 1 Tab1:** Summary of activity costs included in each cost category within the ETAS study

Input/line item	Planning	Training	Community sensitisation	Drug transportation	Drug administration	Supervision	Surveillance	Reporting	Central administration
*Capital Costs*									
Buildings	x	x	x	x	x	x	x	x	x
Communication and IT equipment	x	x	x	x	x	x	x	x	x
Accommodation equipment		x	x		x	x	x		
Vehicles	x	x	x	x	x	x	x	x	x
Other capital	x	x	x	x	x	x	x	x	x
*Recurrent costs*									
Salaried labor	x	x	x	x	x	x	x	x	x
Volunteer labor		x	x		x		x		
Accommodation	x	x	x	x	x	x	x	x	x
Per diem and travel allowances		x	x	x	x	x	x		
Zithromax					x				
Powder oral suspension					x				
Tetracycline eye ointment					x				
Utilities	x	x	x	x	x	x	x	x	x
Personal Protective Equipment	x	x	x	x	x	x	x	x	x
Security services	x	x	x	x	x	x	x	x	x
Communication	x	x	x	x	x	x	x	x	x
Transport/fuel	x	x	x	x	x	x	x	x	x
Vehicle maintenance	x	x	x	x	x	x	x	x	x
Printing	x	x	x	x	x	x	x		x
Laboratory equipment							x		
Other recurrent	x	x	x	x	x	x	x	x	x

Real world costs will be presented in 2 ways: 1) costs related to the programmatic implementation setting (research activities excluded) and 2) costs related to the study setting (including study and implementation costs) (Supplemental Table S1). Study related costs will be helpful in planning future MDA trials within this setting. Cost categories will include capital costs and recurrent costs. Cost activities will include planning, training, community sensitization, drug transportation, drug administration, supervision, surveillance, reporting, and central administration.

The economic cost of capital items, i.e. those only incurred once and with a value of 100 USD or more, will be annualized based on a 3% discount rate and estimates of the useful life of the item [22]. A “useful life” is defined as the period during which an asset or property is expected to be usable for the purpose it was acquired. For vehicles specifically, we will calculate the daily cost of a vehicle in relation to its useful life and discount rate. The financial costs of capital items will be estimated by dividing by the number of years of useful life without discounting (straight line depreciation). Rental costs will be used to determine the cost of office buildings. If a building is owned, the rental cost will be used as a cost indicator. Recurrent costs will be disaggregated from The Carter Center budget and assigned to the cost data categories for each treatment arm after each intervention phase as well as the standard-of-care annual MDA. Personnel costs will include participation in the intervention (e.g., per diems), as well as the relevant share of that person’s salary and fringe benefits that cover their working time as part of the intervention [23]. The proportion of salaries and benefits that are attributable to MDA activities will be estimated by program staff.

Commodities include the study drug, Zithromax®, which is donated, as well as TEO, which is purchased by The Carter Center. The cost of TEO will be included as a financial and economic cost. The economic costs of donated medicines will also be calculated. List costs will be derived from the International Medical Products Price Guide [24].

To estimate the costs associated with a programmatic setting, study and research costs will be removed to make costs comparable to the control communities. These costs would be those associated with increased supervision and monitoring, increased training for data collection, data collection, and administration of the study, and they will be separated among other costs. Further analysis will use the costs associated with the 2 intervention delivery methods and will estimate the potential costs incurred if each intervention was scaled up region- or country-wide. This will be calculated by multiplying the unit cost per person treated by the number of people requiring antibiotics, as stated in the WHO Alliance for the Global Elimination of Trachoma by the year 2020 (GET2020) database [25].

All costs will be presented in constant 2022 USD. If required, costs will be first converted from the local currency to USD, using the World Bank exchange rate relating to the time period during which the cost data were collected. The values will then be inflated using US inflation rates to the base year of the analysis [26, 27].

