#### Economies of scale

Costing analyses of MDA programs often assume an intervention’s cost per treatment is constant, regardless of the number of individuals treated. This is a misleading way to consider the delivery costs of MDA, due to the occurrence of economies/diseconomies of scale [28]. This analysis will explore the effect of economies of scale by presenting the cost per person treated at 3 different coverage levels (60%, 80%, 90%).

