### Community acceptability

#### Antibiotic coverage

Prior to the MDA interventions, a household census will be conducted in all 30 communities whereby all members of all households will be enumerated and the name, sex, and age of everyone will be recorded via electronic census forms. A household member is defined as any person who has lived for at least one month in the household and eats and sleeps in the household. Global positioning system (GPS) coordinates will be captured for each household. The study community census will be used to establish the population to be targeted for study interventions and will provide the denominator for MDA coverage calculations. New residents migrating into study areas after the census but prior to MDA treatment will be added to the census as they are detected. Further, residents unknown to the study team during the MDA treatment will also be added to the census and subsequently treated, if eligible.

During the MDA, each administered dose will be recorded into the electronic record created during the community census by a trained data collector who travels with the distribution team. This record will be used for both study arms to determine the antibiotic coverage during each of the subsequent treatment rounds, allowing for the calculation of the number of doses each participant received. The definition of coverage for this study is: the number of individuals ages 6 months to 9 years who received the drug in study communities in each treatment round divided by the number of children ages 6 months to 9 years enumerated in the baseline census. A secondary analysis will calculate the antibiotic coverage in each round for the age groups 10 to 15 years and ≥ 15 years. Further analyses on compliance will examine the extent and predictors of missed rounds among the 2 study arms.

The dataset on treatment coverage will be compiled quickly by the study coordinator and will be used to monitor the success of the intervention. If the coverage is lower than expected, < 85% among children ages 6 months to 9 years, the treatment team will be redeployed to conduct a community mop-up to improve treatment coverage.

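### Total cost in the triple-dose versus biannual comparison carries chance imbalance in community size, which cost per person treated only partly removes; adjust for the pre-MDA census population

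*Protocol article*

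**What the plan says.** Under 'Study design overview', "The primary outcomes of the study are the cost of enhanced MDA compared to standard-of-care annual MDA", alongside community acceptability. 'Intervention costing' adds that the two enhanced strategies are also compared with each other, and it names two cost measures: "This will be used to identify the cost per person treated and total costs associated with each arm of the study and annual MDA". On the unit of analysis it says "The study will use the community level as the unit of analysis for total costs and calculate the unit cost per person treated". The only size correction described is division by the number of people treated.

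The abstract states that "30 communities will be randomized 1:1 to receive 1 of 2 enhanced MDA interventions", so each enhanced strategy has 15 communities. No stratification, matching or constraint on size is described. 'Surveys and trachoma monitoring' has the 30 communities drawn with equal probability. Entry sets no size criterion: "Communities are eligible to participate if they are in the study county regardless of the individual-community level TF prevalence", and there are no community-level exclusions. A further 15 randomly chosen annual-MDA communities are costed by the same methods.

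Under 'Antibiotic coverage', a household census precedes MDA in all 30 study communities. "The study community census will be used to establish the population to be targeted for study interventions", and it also supplies the coverage denominator. No use of it in the cost comparison is described.

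**The concern.** The population of a community is an obvious candidate driver of what it costs to treat. With 15 communities per strategy and no control of size, one strategy may draw larger communities and look dearer in total for that reason alone.

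The unit cost helps, but completely only if cost is proportional to population. The protocol doubts that itself. Of the assumption that cost per treatment does not vary with the number treated, 'Economies of scale' says: "This is a misleading way to consider the delivery costs of MDA, due to the occurrence of economies/diseconomies of scale". The analysis offered there varies coverage (60%, 80%, 90%), not community size.

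Triple-dose versus biannual is the study's only randomized cost contrast, and it is probably the smaller one. The unit cost is also what 'Intervention costing' multiplies up to regional or national scale, so an imbalance left in it would carry into that projection.

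**Working it through.** **1. The protocol's own figures.** 'Setting, eligibility, and participants' gives a mean population of 649, 40% of it aged 6 months to 9 years. 30 × 649 = 19,470 and 0.40 × 19,470 = 7,788, both as stated. Per community, 0.40 × 649 = 259.6 children (given as 260).

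**2. Contrast implied by treatment counts**, using the rounds under 'Interventions' at full coverage:
- Annual: 649
- Triple-dose: 649 + 2 × 259.6 = 1,168
- Biannual: 2 × 649 = 1,298

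Ratios: biannual/triple-dose 1,298/1,168 = 1.11; triple-dose/annual 1.80; biannual/annual 2.00. These counts are only a proxy for cost.

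**3. Chance imbalance in size.** The 95% half-width of the relative difference in mean size between two groups of 15 is 1.96 × CV × √(2/15), with √(2/15) = 0.365. The protocol gives no CV, so a range is assumed:
- CV 0.3: 0.215
- CV 0.5: 0.358
- CV 0.8: 0.573

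**4. Effect on the observed biannual/triple-dose ratio.** Assumptions: true cost ratio 1.11, lognormal sizes, and a share f of the average community's cost that does not depend on size; 40,000 draws, size variation only. Each cell gives the 95% range and, in brackets, the probability that the ratio falls below 1.

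| CV | f | Total cost | Cost per person |
|---|---|---|---|
| 0.3 | 0 | 0.90–1.38 (17%) | 1.11 (0%) |
| 0.3 | 0.5 | 1.00–1.24 (3%) | 1.00–1.24 (3%) |
| 0.3 | 0.8 | 1.06–1.16 (0%) | 0.94–1.32 (11%) |
| 0.5 | 0 | 0.78–1.59 (29%) | 1.11 (0%) |
| 0.5 | 0.5 | 0.93–1.33 (12%) | 0.93–1.33 (12%) |
| 0.5 | 0.8 | 1.03–1.19 (0.2%) | 0.83–1.48 (24%) |
| 0.8 | 0 | 0.64–1.94 (36%) | 1.11 (0%) |
| 0.8 | 0.5 | 0.84–1.47 (23%) | 0.84–1.47 (23%) |
| 0.8 | 0.8 | 0.99–1.24 (3.5%) | 0.71–1.74 (33%) |

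The two measures fail at opposite ends. Total cost is exposed when cost scales with size, and cost per person when it does not. At f = 0.5 they are equally exposed.

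**5. Effect of adjustment.** With 20% residual noise added on the log scale, f from 0 to 0.5 and CV from 0.3 to 0.8, the SD of the estimated log cost ratio is about:
- crude total cost: 0.09–0.27
- cost per person treated: 0.07–0.16
- total cost adjusted for log population: 0.07–0.08

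The adjusted estimate hardly changes with CV or f. At f = 0 it gains little over cost per person. Adjustment does not make an 11% difference easy to detect: at an SD of 0.075 the 95% half-width is 1.96 × 0.075 = 0.147, against log 1.11 = 0.10.

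**6. Same check against annual MDA.** With total cost proportional to size (f = 0), triple-dose/annual spans 1.45–2.23 at CV 0.3 and 1.26–2.56 at CV 0.5, with a wrong-direction probability below 0.1%. That probability is 2% at CV 0.8 and 5% at CV 1.0. For biannual/annual it is about 1% and 2.5%.

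**The case against.** **No model is stated.** The article gives no test, interval or regression for cost and does not say that the comparison is unadjusted. Covariates are commonly left to the full protocol or analysis plan, neither of which is shown. This stands: the point is an improvement to a stated measure and unit, not an error in the text.

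**Annual MDA.** A reader might infer that size imbalance could swamp the contrast with annual MDA, which is the one named as the primary outcome. The documents do not support that. Implied ratios of 1.8 to 2.0 are rarely reversed, although they would be imprecisely estimated.

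**Direction of scale effects.** A reader might also infer that the strategy with larger communities gets a lower unit cost. The protocol speaks of both economies and diseconomies of scale and leaves the direction open.

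**Size is already handled in part.** Cost per person treated is reported and used for scale-up, and cost drivers are varied in sensitivity analyses. This is right as far as it goes. When cost is proportional to size, the unit cost does the whole job.

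**Costs may be allocated rather than observed.** Recurrent costs are disaggregated from the implementing partner's budget, and salary shares are estimated by staff. A regression of allocated cost on population could partly return the allocation rule. This stands and limits the fix.

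**No census for annual MDA.** The census is described only for the 30 study communities, and no community-level populations are shown for the other 15. This also stands.

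**Conclusion.** The point holds for triple-dose versus biannual. Chance imbalance in mean size of about ±21% to ±57% (assumed CV 0.3 to 0.8) is large beside an approximately 11% contrast in treatments, and neither planned measure is protected across plausible cost structures. Adjusting for a baseline value already collected brings the SD of the log cost ratio to about 0.07–0.08, against up to 0.27 for crude total cost and 0.16 for cost per person.

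It is a worthwhile gain in precision, not a flaw that invalidates the costing. Its size rests on three assumptions absent from the protocol: the spread of community size, the share of cost independent of size, and the residual noise. The 11% also rests on treatment counts. Per-round delivery costs could make the true contrast larger, smaller or opposite in sign.

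**What to change.** In 'Intervention costing':

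- Keep crude totals and cost per person treated.
- Add a triple-dose versus biannual comparison of community-level total cost adjusted for pre-MDA census population, for example log cost regressed on strategy and log population. Report the cost ratio with its 95% interval, and the predicted cost of each strategy at a common community size such as 649.
- Apply the model to costs recorded at community level. Show costs allocated pro rata from the central budget separately.
- Extend it to annual MDA only if the programme holds community-level population figures from one source for all 45 communities.

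The price is one degree of freedom, a few sentences and a little extra analysis. The randomized comparison needs no new population data. Separating recorded from allocated costs takes some work in the costing database.
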